### Measures

3.4

Each participant will be asked to respond to 8 validated neuropsychological scales assessing stress (Perceived Stress Scale, PSS), anxiety and depression (PHQ-4), joy predisposition (DPES-Joy Subscale), mindfulness awareness (MAAS), resilience (BRS), mental well-being (WEMWBS), and post-traumatic growth (PTGI). PSS is defined as the primary outcome while BRS is the key secondary outcome.

**Questionnaires**. The following questionnaires are incorporated into the study survey and will be administered to the study participants:

*Perceived Stress Scale (PSS).* PSS is a 10-question validated instrument that assesses stress. Participants are asked to rate on a scale of 0 (never) to 4 (very often) how often they agree with various statements designed to assess the degree to which life situations are appraised as stressful. Items from each of the 10 questions are then summed to create a total perceived stress score.

*4 Item-Patient Health Questionnaire measuring Anxiety and Depression (PHQ-4).* Four questions rated on a scale of 0 (Not at all) to 3 (Nearly every day). The sum is computed for the responses and scores range from 0 to 12. Categories of psychological distress are classified as: None (0–2 score), Mild (3–5 score), Moderate (6–8 score) and severe (9–12 score). Anxiety subscale is calculated by measuring sum of item 1 and 2 (score range, 0–6; scores greater than 3 considered positive for anxiety screening.) Depression subscale is calculated by measuring sum of item 3 and 4 (score range, 0–6; scores greater than 3 considered positive for depression screening.)

*Dispositional Positive Emotion Scale- Joy Subscale (DPES-Joy).* The joy subscale of DPES is a 6-item questionnaire that measures a dispositional tendency to feel joy in life. Participants report their level of agreement to each item on a scale of 1 (Strongly agree) to 7 (Strongly disagree) and a mean score is calculated.

*Mindfulness Attention Awareness Scale (MAAS)- short form.* MAAS - short form is a 5-question validated instrument that assesses mindfulness and attention while performing routine activities of daily living. Participants are asked to rate on a scale of 1 (Almost Always) to 6 (Almost Never) the frequency of occurrence for each experience. A mean score is then computed using items from each of the 5 questions to calculate the individual's MAAS score.

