*Brief Resilience scale (BRS).* The BRS identifies an individual's ability to “bounce back” or recover from a stress. This 6-item scale is rated on a 5-point response scale (1 = Strongly disagree; 5 = Strongly agree). Responses from each of the 6 questions are summed to create a total score, producing a range of 6–30. The score is divided by the number of questions answered to calculate the individual brief resilience score.

*Warwick- Edinburgh Wellbeing Scale (WEMWBS).* The purpose of the WEMBS scale is to assess various aspects of mental health such as positive affect, satisfying interpersonal relationships, and positive functioning. This 14-item scale is rated on a 4-point response scale (1 = none of the time to 4 = all of the time). Response from each of the 6 questions is then summed to create a total wellbeing score.

*Post Traumatic Growth Inventory (PTGI).* The purpose of the PTGI is to capture the positive outcomes reported by a person who has experienced a traumatic event. This scale will be administered only to those participants who report being hospitalized during the COVID-19 pandemic. The scale helps to determine a respondent's coping ability in the aftermath of a trauma, their perceptions of self and others, and meaning of the event. This 21-item scale is rated on a 6-point Likert response scale and response to each question is summed to create a total PTGI score.

*Activity Diary.* The weekly activity diary is a tool which helps the participants to keep a track of their activities each week. This enables the study team to measure compliance and protocol adherence by the participants. Based on the construct of the study, we have 2 different activity diaries employed for data collection in this study. The activity diary for seasoned yoga practitioners collects information on their routine activity practiced, its frequency and duration. The activity diary for controls collects information on the activity suggested by study team (the Simha Kriya yoga practice vs placebo activity choices of reading or remaining idle).

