### Analysis

3.6

Baseline characteristics of participants will be recorded. Continuous data will be presented as means ± standard deviation or median (interquartile range) depending on the distribution of the data and assessed with a parametric paired *t*-test or non-parametric Wilcoxon signed rank test, as appropriate. Normality will be assessed with the Shapiro-Wilk test. Categorical data will be presented as frequencies and percentages and assessed with a chi-square or Fisher's exact test, as appropriate. All primary analyses will be assessed using intention-to-treat principles. SAS 9.4 (SAS Institute Inc., Cary, NC) will be used for all analyses with two-sided p-values < 0.05 considered statistically significant.

Aim 1 Analysis. To quantitatively assess the effects of Isha yoga practices between seasoned practitioners and the control groups on measures such as perceived stress, resilience, and overall wellbeing by use of validated scales at baseline, 6 weeks and 12 weeks. We have defined Perceived Stress Score as our primary outcome and Brief Resilience Scale scores as our key secondary outcome. Given the continuous nature of the scales used to assess stress, resilience and measures of well-being, differences between groups will be assessed with a parametric or non-parametric *t*-test. Multivariable regression may be utilized to adjust for potential confounders that deem to vary between the groups based on the univariable analysis prior to that. The distribution of the dependent variable will depend on the actual distribution of the scales recorded in the study. A mixed effect approach in modeling will address the similarity of the subjects enrolled in the study as friends or by matching, by assigning a random intercept to each cluster of related subjects. To assess whether there are differences between baseline and at six weeks, we will employ the use of paired t-tests or non-parametric tests for univariable analysis, as appropriate. Additionally, the change in scales over time can be compared between the groups using mixed models approach, wherein an indicator of time (baseline/6 weeks) will define the direction and significance of the change in a model, adjusted independent of other factors.

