After reviewing the data that was collected over the 12 week period, several amendments were made to the protocol. For example, we compared the three groups, Group 1: Simha-Kriya Yoga for a period of 12 weeks, Group 2: Reading activity/Sitting idle for a period of 12 weeks, and the Yoga Practitioners, rather than the combination of control groups with the yoga practitioners. We also performed Poisson regression rather than linear regression to account for potential confounders due to the distribution of the primary outcomes, PSS and BRS scores. These changes were towards a more conservative approach which we believe provided more valid inference.

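### Poisson regression is a poor model for the bounded PSS and BRS scores: unless dispersion is estimated or a robust variance is used, the adjusted standard errors are wrong and the claim of conservatism is unsupported

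*Protocol article*

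**What the plan says.** Measures (3.4) defines both scores. PSS has ten items rated 0 to 4: "Items from each of the 10 questions are then summed to create a total perceived stress score". The total therefore runs from 0 to 40. BRS has six items rated 1 to 5, with a sum of 6 to 30, and then: "The score is divided by the number of questions answered to calculate the individual brief resilience score". The resulting score lies between 1 and 5 and is usually not an integer. PSS is the primary outcome and BRS the key secondary outcome.

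Analysis (3.6) plans t-tests or non-parametric tests between groups, and reasons from the scale type: "Given the continuous nature of the scales used to assess stress, resilience and measures of well-being". Multivariable regression is optional, to adjust for confounders, with a random intercept per cluster of related subjects. The distribution is left open: "The distribution of the dependent variable will depend on the actual distribution of the scales recorded in the study".

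The last paragraph of that section then reports what was done: "After reviewing the data that was collected over the 12 week period, several amendments were made to the protocol". One amendment compares three groups instead of pooling the controls. The other concerns the model: "We also performed Poisson regression rather than linear regression to account for potential confounders due to the distribution of the primary outcomes". The paragraph ends: "These changes were towards a more conservative approach which we believe provided more valid inference". It does not say how the variance was estimated or which BRS score was modelled. It also lists BRS among the primary outcomes, which disagrees with the two statements elsewhere that it is key secondary.

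**The concern.** Poisson regression is built for counts, and with model-based standard errors it sets the variance equal to the mean. A bounded questionnaire score has no reason to obey that relation. The relation also depends on the unit of measurement, so the error can run in opposite directions for the two outcomes.

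At stake are the adjusted p-values and confidence intervals for the primary and key secondary outcomes. The adjusted model matters here because seasoned practitioners were not randomized against the controls, so that comparison depends on adjustment. A reader told that the method is conservative would trust a significant adjusted PSS result more than may be warranted, and might read a null BRS result as evidence of no effect.

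**Working it through.** The article gives no mean, SD, sample size or effect for either scale, so there is no figure of its own to reproduce. The score ranges and the two-sided 5% level come from the article. All means, SDs, differences and group sizes below are assumptions. Steps 1 to 4 assume model-based Poisson errors; step 5 removes that assumption.

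**1. Dispersion.** Let φ = SD²/mean. The model-based error is the true one divided by √φ: too small if φ > 1, too large if φ < 1. The actual type I error of a nominal 5% test is 2 × [1 − Φ(1.96/√φ)].

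**2. PSS (0–40).** φ exceeds 1 once SD > √mean, which is 3.2, 3.9 and 4.5 at means 10, 15 and 20. At mean 15:

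| SD | φ | Actual type I error |
|---|---|---|
| 3 | 0.60 | 0.011 |
| 4 | 1.07 | 0.058 |
| 5 | 1.67 | 0.129 |
| 6 | 2.40 | 0.206 |
| 7 | 3.27 | 0.278 |
| 8 | 4.27 | 0.343 |

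Over means 10–20 and SDs 5–8 the range is 0.08–0.44; at SD 3 it is 0.004–0.039. A simulation with rounded, clipped scores (mean 15, SD 6, 100 per group) gave 0.22.

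Is an SD above 3.9 plausible? The ten items address one construct and should correlate. With item SD 1 (assumed) and average inter-item correlation r, the variance of the sum is 10 × (1 + 9r). It exceeds 15 once r > 0.5/9 ≈ 0.06.

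**3. BRS on the 1–5 score.** The bounds all but force φ below 1. A flat spread over the whole range has variance (5 − 1)²/12 = 1.33 and mean 3, so φ = 0.44. At a sample size where the linear model has 80% power, Poisson power is about Φ(2.80 − 1.96/√φ), or roughly 44% for the flat spread. At an assumed mean of 3.4:

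| SD | φ | Poisson power |
|---|---|---|
| 0.7 | 0.144 | 0.01 |
| 0.8 | 0.188 | 0.04 |
| 0.9 | 0.238 | 0.11 |

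Simulation at these values (100 per group) ran somewhat lower, at 0.005–0.057.

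Power depends on group size. For mean 3.5, SD 0.75 and a difference of 0.3, closed-form Poisson power is 0.02 at 100 per group (linear model 0.81), 0.19 at 200, 0.50 at 300, 0.78 at 400 (simulated 0.68) and 0.92 at 500.

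**4. BRS on the 6–30 sum, and the unit problem.** At mean 21 and SD 4.5, φ = 20.25/21 = 0.96. Simulated type I error was 0.04, and power 0.76 against 0.80 for least squares. Over sum means 18–24 and SDs 3–6, the type I error ranges from 0.001 to 0.17.

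For participants who answer all six items, dividing by 6 changes no information. It leaves the log ratio unchanged but multiplies its model-based variance by 6, so z falls by √6 = 2.45. A z of 3.0 (p = 0.003) on the sum becomes 3.0/2.45 = 1.22 (p = 0.22) on the 1–5 score.

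**5. Same simulated data, other errors.** With 100 per group, Poisson with a robust variance and least squares both gave type I error of about 0.05–0.06 for PSS and 0.06 for BRS on the 1–5 score. BRS power for a difference of 0.3 was 0.79, against 0.01 with plain Poisson.

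**The case against.** The strongest reply is that everything in steps 1 to 4 needs the plain model-based variance. The article says only that Poisson regression was performed, and a condensed article may leave the variance estimator to a fuller document. A log-link Poisson estimating equation with robust variance is legitimate for non-negative, non-integer outcomes, and its z-value does not change with the scoring unit. This stands, so the conclusion has to be conditional.

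Four further points have weight.

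- A reader might infer that the PSS p-values are too small as a matter of fact. The article gives no SD, and at an SD near 3 the test would be conservative. Covariates and the cluster intercept would also lower the residual variance somewhat.
- A reader might infer that the BRS test has almost no power. That needs the 1–5 score and modest groups. The article states no sample size and does not exclude the 6–30 sum.
- A reader might infer that the 5% level fails for the primary outcome as a whole. Poisson regression replaced the optional adjusted model; the planned unadjusted t-tests were not withdrawn.
- The conservatism claim covers both amendments, including the three-group comparison, and plain Poisson is indeed conservative for BRS on the 1–5 score.

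The plan did foresee choosing the distribution from the data, so a change of model is not in itself a breach. But that clause does not make a count model suitable for these scores. Nor does the planned random intercept: it absorbs only between-cluster variance and cannot correct underdispersion.

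**Conclusion.** The point holds in conditional form. The article names a count model for the adjusted analysis of two bounded scores that it elsewhere treats as continuous, and justifies it with a claim that its own score definitions do not support. Unless dispersion was estimated or a robust variance used, the adjusted standard errors are wrong.

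The likely direction for PSS is too small, with a rejection rate of about 13–34% under the null at an assumed mean of 15 and SD of 5–8. For BRS on the 1–5 score it is too large, with about 1–11% power where 80% was available, at an assumed mean of 3.4 and SD of 0.7–0.9.

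The blanket description as more conservative is therefore unsupported, and for the primary outcome in the adjusted model it is probably reversed. The documents do not show that any reported p-value is actually wrong. Correction is warranted before the adjusted results are relied on.

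**What to change.** Analyse PSS and BRS with a linear mixed model with robust (sandwich) standard errors, and report mean differences in scale points with 95% confidence intervals. If the log link is kept, use a robust variance or an estimated dispersion, never the model-based Poisson standard error. State which variance estimator was used and whether the BRS sum or the 1–5 score is modelled. Delete the claim that this change is more conservative, and describe BRS consistently as key secondary.

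The cost is one re-run of the models and a change of wording, with no new data. PSS confidence intervals will probably be wider. If a robust or scaled variance was already used, the remedy reduces to saying so, naming the BRS score and removing the claim.

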## Discussion

4

The COVID-19 pandemic has placed significant stress on individuals, families, and communities. Psychological distress, depression, sedentary lifestyles, and decreased overall wellbeing are on the rise. Even prior to the pandemic, depression and anxiety were the leading source of adult disability worldwide [36,37]. Yogic practices which include breathing, meditation, and postures, have shown promise as a mechanism for improving mental and physical health. In a meta-analysis of 41 trials, researchers found evidence that meditation reduced multiple negative dimensions of psychological stress such as anxiety and depression [38]. In a systematic review [39] which investigated the effects of yoga on sympathetic nervous system and hypothalamic pituitary adrenal axis regulation measures, evidence suggested that yoga practice led to improved regulation of these systems and decreased depression and anxiety symptoms. Similarly, in a recent study of a yogic breathing protocol on emotion processing, anxiety, and affect, thirty individuals were assessed at baseline and after 4 weeks of practice [40]. Functional magnetic resonance imaging (MRI) showed significantly decreased states of anxiety and negative affect at follow-up, and the modulation of activity in brain regions involved in emotional processing, attention, and awareness.

In this study, we will compare the effects of yoga practices between seasoned yoga practitioners and two controls who are age ( ±3 years) and gender matched and living in the same neighborhood. This randomized controlled trial will compare seasoned yoga practitioners to non-meditators who have been randomized into active comparator vs placebo comparator arms on various outcome measures including perceived stress, resilience, wellbeing, and protection and recovery from COVID-19. Though time and funds were limited for this particular study, in the future we hope to include additional wellness measures such as sleep duration and quality, as well as objective measures of compliance such as Fitbit.

We hypothesize that routine yoga practice during the COVID-19 pandemic will reduce stress, enhance well-being, and provide protective effects against COVID-19. While a direct comparison between seasoned yoga practitioners and non-meditators at baseline would have been sufficient to establish the effectiveness of yoga practices; the dynamic progression of COVID in varying geographical regions at different rates warranted these comparisons at least at two other time points separated by 6 weeks each. Furthermore, by incorporating a robust short (3 min) breathing yoga activity into the non-meditator cohort in a randomized fashion, we aimed to establish that exposure to any yoga practice will significantly improve mental health status in non-meditators. With the growing concern about the physical and mental impacts of COVID-19 and increased interest in alternative practices such as yogic techniques, this study will contribute to the growing body of evidence about the safety and efficacy of yoga for emotional, mental, and physical health conditions.

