## Abstract

**Objectives:**

The COVID-19 pandemic has been a significant stressor worldwide and reports of psychological distress, depression, sedentary lifestyles, and overall decreased wellbeing are increasing. Yoga practices have been found to improve mental and physical health. The purpose of this randomized controlled trial is to compare Isha yoga practitioners to controls on perceived stress, resilience, wellbeing, and protection and recovery from COVID-19. Trial Design. In this prospective randomized control trial, the effects of yoga practices are being compared between seasoned yoga practitioners with two controls who are age (±3 years), gender matched, and living in the same neighborhood.

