## **Objectives.** The purpose of this randomized controlled trial is to accomplish the following specific aims

**2**

Specific Aim 1: To quantitatively assess the effects of Isha yoga practices between seasoned practitioners and control groups on perceived stress, resilience, and wellbeing by use of validated scales.

Specific Aim 2: To compare protection and recovery from COVID-19 infection between seasoned Isha yoga practitioners and controls as demonstrated by:a.Self-reported duration of fever and respiratory symptoms in COVID-19 positive participantsb.Self-reported readiness to return to work (or a feeling of being physically and mentally fit)

Specific Aim 3: To compare prevalence rates of diagnosed COVID-19 infection between the seasoned Isha yoga practitioners and age and gender matched controls at baseline, 6 weeks and 12 weeks.

We hypothesize that routine yoga practice during the COVID-19 pandemic will reduce stress and enhance well-being.

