### Intervention description and timing

3.2

This is analytic study wherein an observational arm of ‘seasoned yoga practitioners’ is being compared with age, gender, and region matched ‘non-meditators’ as controls. The non-meditators control group is further randomized to active comparator arm and placebo comparator arm.

Control participants or Non-meditators are individuals with minimum (<1 month) to no yoga practice of any kind, prior to study enrollment. Non-meditator controls randomized to an ‘Active comparator arm’ are taught a 3 min yoga practice (Simha Kriya) which involves deep breathing exercises and meditation following randomization. Within the yogic tradition, there are breathing exercises which are considered to foster pranayama, which builds a type of “armor” or Kavacham for oneself against negative impacts encountered in the every day world. Prana is considered the fundamental energy and the foundation for all life. Pranayanic practices have been shown to contribute to positive physiologic and psychologic changes including improvements in hypertension, cognitive function, breathing frequency, stress, and heart rate variability [13,[32], [33], [34]]. In a study of another Isha pranayama practice, Peterson et al. found that after 6 weeks of daily practice, participants reported improved general well-being (General Well-Being Scale) and lower levels of perceived stress (Perceived Stress Scale) [35]. In the current study, the Simha Kriya practice will be taught on-line by highly-trained Isha practitioners and participants are asked to perform Simha Kriya using a web-based application, twice per day.

The other control group acts as a ‘Placebo comparator arm’ and performs either reading activities or remaining idle for 15 min a day throughout the study period. Respondents in the observational arm (seasoned yoga practitioners) continue their usual yoga practices. Please see Fig. 1 for study flow chart. Participants aged <18 years or >80 years will excluded from the study. Please see Table 1 for additional Inclusion/Exclusion Criteria.

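### All three Specific Aims rest on a non-randomised comparison of practitioners with controls that is labelled a randomised trial and said to suffice for effectiveness; the one randomised contrast has no Specific Aim and no designated primary analysis

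*Protocol article*

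**What the plan says.** **Label.** The Abstract states: "The purpose of this randomized controlled trial is to compare Isha yoga practitioners to controls on perceived stress, resilience, wellbeing". The heading of section 2 (Objectives) also uses the randomised-trial label, and the Discussion repeats it: "This randomized controlled trial will compare seasoned yoga practitioners to non-meditators who have been randomized into active comparator vs placebo comparator arms".

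**Aims.** Every numbered aim in section 2 is a practitioner-versus-control contrast:
- Aim 1: "To quantitatively assess the effects of Isha yoga practices between seasoned practitioners and control groups on perceived stress, resilience, and wellbeing"
- Aim 2: "To compare protection and recovery from COVID-19 infection between seasoned Isha yoga practitioners and controls"
- Aim 3: "To compare prevalence rates of diagnosed COVID-19 infection between the seasoned Isha yoga practitioners and age and gender matched controls"

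Section 3.6 (Analysis) restates the same contrasts and adds: "All primary analyses will be assessed using intention-to-treat principles".

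**Who is randomised.** Section 3.2 describes the practitioners as an observational arm and then says: "The non-meditators control group is further randomized to active comparator arm and placebo comparator arm". Section 3.5 (Randomization) confirms that only non-meditators are allocated, to Simha Kriya or to reading/idle.

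**How groups are formed.** Under section 3.1, practitioners come through the Isha Foundation's channels and must already be trained and practising regularly. Controls are friends they nominate. Where nobody is nominated, the study team matches on location.

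**Inference claimed.** The Discussion asserts that "a direct comparison between seasoned yoga practitioners and non-meditators at baseline would have been sufficient to establish the effectiveness of yoga practices".

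**The concern.** The practitioner group consists of people who took up yoga, found it worth continuing and then volunteered through the school. Whatever leads people to do that (for example outlook, health, income or earlier stress) may also be related to perceived stress and resilience. A baseline difference between such people and non-meditators mixes any effect of practice with selection into it. Calling the comparison a randomised trial, and calling the baseline contrast sufficient for effectiveness, attaches a causal reading to the part of the design that cannot carry one. The comparison that can carry one, Simha Kriya versus reading/idle, is not named in any Specific Aim or designated as a primary analysis. A reader could then take an observational association as the trial's randomised result.

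**Working it through.** **Textual check.** The article states no sample size, SD, effect size or power, so there is no figure of its own to reproduce. The relevant statements compare as follows.

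| Question | Where | Finding |
|---|---|---|
| What do the aims compare? | Section 2; section 3.6 | Practitioners versus controls in Aims 1, 2 and 3 |
| Is anyone assigned to be a practitioner? | 3.1, 3.2, 3.5 | No; practitioners are already practising and continue as usual |
| What is randomised? | 3.2, 3.5 | Non-meditators only: Simha Kriya or reading/idle |
| What is the practitioner contrast called? | Abstract, section 2 heading, Discussion | A randomised controlled trial |
| What is it called in Methods? | 3.2 | A comparison with an observational arm |
| Where does the randomised contrast appear? | Discussion; end of 3.6 | A stated intention; an exploratory three-group dose-response analysis; a three-group comparison adopted after the 12-week data were reviewed |

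Two things follow.

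1. The randomised label contradicts section 3.2. Intention-to-treat analyses people as assigned. Aim 1, which carries the primary outcome (PSS), has one side to which nobody was assigned.
2. The practitioners' baseline score is measured after their exposure began, because regular practice is an entry condition. There is no pre-exposure score to adjust for.

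**Illustration of size.** Inputs:
- From section 3.6: two-sided alpha 0.05.
- From sections 3.1 and 4: two controls sought per practitioner.
- Assumed: the number of practitioners n, and a pre-existing group difference of d SD. True yoga effect is set to zero.

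With n practitioners and 2n controls, SE = √(1/n + 1/(2n)) in SD units, and

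P(p<0.05) = Φ(d/SE − 1.96) + Φ(−d/SE − 1.96).

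For n = 100, SE = √(0.010 + 0.005) = √0.015 = 0.1225.
- d = 0.2: d/SE = 1.633, so P = Φ(−0.327) + Φ(−3.593) = 0.372.
- d = 0.3: d/SE = 2.449, so P = Φ(0.489) + Φ(−4.409) = 0.688.

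| Practitioners / controls (assumed) | d = 0 | d = 0.2 | d = 0.3 |
|---|---|---|---|
| 50 / 100 | 5% | 21% | 41% |
| 100 / 200 | 5% | 37% | 69% |
| 200 / 400 | 5% | 64% | 93% |

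A larger sample makes the false conclusion more likely, because it does nothing to the bias. The formula treats the groups as independent and ignores matching, so it shows the order of size only.

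**The case against.** **The design is disclosed.** Sections 3.2 and 3.5 say plainly who is observed and who is randomised. This stands: the fault is an internal contradiction in labelling, together with one unsupported claim. A reader might infer that the design is concealed, and the article does not support that.

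**Confounding is addressed.** Controls are matched on age, gender and area. Section 3.6 allows multivariable adjustment and random intercepts for related subjects, and its closing paragraph reports a Poisson regression to account for confounders. These help, but they do not remove self-selection into sustained practice. The planned adjustment is optional and chosen by univariable screening, and no pre-exposure measure exists. Comparing change over time removes stable differences in level, but practitioners do not start their practice within the study, so their change does not measure the effect of taking it up.

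**The randomised contrast does have a purpose.** The Discussion states an intention to show benefit of a short practice in non-meditators, allocated at random. So a reader who concludes that it has no aim at all goes too far. What is absent is a numbered Specific Aim and a designated primary analysis.

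**Controls are not only friends.** Section 3.1 provides for location matching by the study team. This does not make the contrast randomised.

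**Pooling.** A reader might infer that the practitioner-control difference is still diluted because half the controls practise yoga. The end of section 3.6 says the combined control group was replaced by a three-group comparison, so this is not a live consequence. A figure of one half would also need 1:1 allocation, which section 3.5 does not state.

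**The numbers are assumed.** True. Neither the sample size nor the size of any bias comes from the article, and the table does not show that a bias of that size exists here.

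**Conclusion.** The point holds, limited to labelling, inference and the standing of the randomised contrast. The practitioner-control comparison in all three Specific Aims is observational. The randomised label for it contradicts section 3.2, and the claim that a baseline comparison would establish effectiveness is wrong as written. That conclusion rests on the text alone. The illustration (about 37% and 69% false-positive results at 0.2 and 0.3 SD, with 100 versus 200 assumed and no yoga effect) shows only that modest selection is enough to produce a significant difference.

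A reader might also infer that Simha Kriya versus reading/idle can simply be declared primary at one follow-up visit. The article does not support that step: section 3.6 says the two arms were separated after the 12-week data were reviewed, so choosing a visit now could be guided by results.

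**What to change.** 1. Delete the Discussion's statement that a baseline comparison would have been enough to establish effectiveness.
2. In the Abstract, section 2, section 3.6 and the Discussion, describe practitioners versus controls as an observational matched comparison that yields adjusted associations. Reserve the randomised label and the intention-to-treat statement for the non-meditators.
3. Add an explicit aim for Simha Kriya versus reading/idle on PSS, with all randomised non-meditators analysed as randomised, and state that it is the only contrast supporting a causal statement.
4. Report that contrast at both 6 and 12 weeks, not at one visit chosen now. Unless the full protocol shows otherwise, disclose that its status was set after data review, and give the randomisation as the reason for it.
5. Report the originally planned comparison, with the control arms combined, beside it.

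No new data are needed: the cost is rewording the aims, analysis and conclusions, plus reporting both sets of results. The real price is a weaker claim about long-term Isha practice, which becomes an association.
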